## Background

In patients with stage III cutaneous melanoma, adjuvant treatments with PD-1 and BRAF+MEK inhibitors were approved based on improved recurrence-free survival (RFS) [1–3]. None of the adjuvant trials have yet demonstrated any benefit in overall survival (OS) while the OS data from the European Organisation for Research and Treatment of Cancer (EORTC) 1325/KEYNOTE-054 study are still awaited [4–6]. A population-based registry study from Sweden reported no significant differences in OS after the national implementation of adjuvant treatments in 2018 [7]. At the European Society for Medical Oncology (ESMO) meeting in September 2022, the results from the phase II SWOG S1801 study were presented, demonstrating significantly improved event-free survival (EFS) with neoadjuvant and adjuvant PD-1 inhibitors compared to only adjuvant anti-PD-1 [8]. Subsequently, already in October 2022, neoadjuvant treatment with PD-1 inhibitor monotherapy was implemented on a national level in Sweden [9]. The phase II PRADO (Personalized Response-driven Adjuvant combination therapy) trial further demonstrated the feasibility and clinical utility of a response-adapted approach in which pathologic response to neoadjuvant immune checkpoint blockade guided subsequent adjuvant therapy and surgical management. This strategy substantially reduced the need for therapeutic lymph node dissection (TLND) and adjuvant systemic treatment in patients achieving major pathologic response (MPR) [10]. Furthermore, at the American Society of Clinical Oncology (ASCO) meeting in June 2024, the results from the phase III NADINA study were presented, demonstrating improved EFS in patients receiving anti-PD-1 and anti-CTLA-4 combination as neoadjuvant treatment, with subsequent adjuvant therapy tailored according to pathologic response [11]. At present there are hence two studies demonstrating superiority with neoadjuvant compared to adjuvant treatment only, but no clinical trial has compared neoadjuvant PD-1 inhibitor monotherapy to PD-1 and CTLA-4 inhibitor combination therapy.

## Methods

### Aim

Two studies (SWOG S1801 and NADINA) have demonstrated superiority when using neoadjuvant treatment compared to adjuvant treatment only, but no study has compared anti-PD-1 monotherapy (SWOG 1801 regimen) to anti-PD-1/anti-CTLA-4 combination (NADINA regimen) therapy. The SWE-NEO study is a phase III randomised controlled multi-centre open-label trial, that aims to compare these two regimens in a response-guided approach, where the PD-1/CTLA-4 inhibitor combination is potentially more effective but also associated with more side effects.

### Study population

The study population includes patients with resectable stage III cutaneous, acral or unknown primary melanoma who are candidates for the neoadjuvant treatment procedure. Patients must be naïve to CTLA-4/PD-1/PD-L1 blockade and BRAF+MEK inhibition, and at least 18 years of age.

### Inclusion criteria

Age ≥ 18.Signed and dated written informed consent.Eastern Cooperative Oncology Group (ECOG) performance status of 0–1.Patients must meet all the following criteria:Histologically or cytologically confirmed stage III melanoma. In the case of in-transit metastases (with or without lymph node metastases)‚ ≤ 3 resectable in-transit metastases are permitted.Patients with cutaneous, acral, or unknown primary melanomas are eligible for enrolment.Resectable tumours are defined as having no significant vascular, neural, or bony involvement, and for which complete surgical resection with tumour-free margins can be safely achieved.No history of other malignancies, except if treated with curative intent and with a cancer-related life expectancy of more than 5 years.No prior therapy targeting CTLA-4, PD-1 or PD-L1.No prior therapy targeting BRAF and/or MEK.

### Exclusion criteria

Unresectable melanoma.Uveal/ocular or mucosal melanoma.Any serious or uncontrolled medical conditions that, in the investigator’s opinion, may increase the risk associated with study participation or study drug administration, impair the subject’s ability to receive protocol therapy, or interfere with the interpretation of study results.Any condition requiring systemic treatment with corticosteroids (>10 mg daily prednisone equivalents) or other immunosuppressive medications within 14 days prior of study drug administration.Women who are pregnant or breastfeeding. Patients with childbearing potential must agree to safe contraception.Any condition that may hamper compliance with the study protocol and follow-up schedule.

### Endpoints

The primary endpoint is EFS, defined as time from randomisation to melanoma progression (unresectable stage III or stage IV disease), melanoma recurrence, or death from any cause (treatment-related, melanoma related or any other).

The secondary endpoints of the SWE-NEO trial are:

RFS, defined as the time from the date of surgery to the date of melanoma recurrence, treatment-related death or melanoma-related death, whichever occurs first.Distant metastasis-free survival (DMFS), defined as the time from the date of randomisation to the date of first distant metastasis, treatment-related death or melanoma-related death, whichever occurs first.OS, defined as time from the date of randomisation to the date of death from any cause.MPR, defined as ≤10% viable tumour cells in the excised tumour.Correlation of pathologic response in each arm to RFS, DMFS, and OS.Correlation of radiological and clinical response evaluation to RFS, DMFS, and OS.Proportion of patients having surgery according to protocol-defined timing (within 10 weeks from first neoadjuvant treatment course).Surgical complication rates graded according to Clavien-Dindo surgical classification.Frequency and duration of all grade and grade 3–5 treatment- related adverse events (AEs), graded according to Common Terminology Criteria for Adverse Events (CTCAE) 5.0.

Explorative endpoints include different biological markers analysed from sequential blood and tumour samples and their correlation with treatment efficacy and safety. The following will be studied as potential biomarkers:

Circulating tumour DNA (ctDNA) in plasma.Extracellular vesicles (EVs) in plasma.Multiparameter flow cytometry, and to profile immune cells in peripheral blood mononuclear cells (PBMC) isolated from blood.Single cell analyses of tumour and blood samples including single cell RNA sequencing and T cell and B cell receptor profiling to determine predictive biomarkers.Tumour spatial transcriptomic analyses to determine tumour architectural features that associate with pathological response and EFS.

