### Study intervention

Patients will be randomised after a diagnosis of resectable stage III melanoma to receiving either two cycles of intravenous infusion with ipilimumab 80 mg plus nivolumab 240 mg (combination therapy administered at 3-weeks interval) or two cycles of intravenous infusion with nivolumab 480 mg (monotherapy administered at 4-weeks interval) (Figure 1). In both groups, the two neoadjuvant treatment courses will be followed by an index node resection (in patients with lymph node metastases) or radical surgery for in-transit metastases. Patients with MPR, receive no further treatment and will enter follow-up. In the absence of MPR, patients with lymph node metastases undergo TLND and then receive adjuvant treatment, nivolumab 480 mg (Q4w x12), or if harbouring BRAF V600E tumour mutation, 46 weeks of dabrafenib 150 mg x2 and trametinib 2 mg 1×1.

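### RFS is timed from surgery but patients are randomised before neoadjuvant treatment, so a between-arm RFS comparison is conditional on surgery and not randomised

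*Protocol article*

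**What the plan says.** On timing, the Study intervention section of the protocol article states: "Patients will be randomised after a diagnosis of resectable stage III melanoma". Surgery comes later: "In both groups, the two neoadjuvant treatment courses will be followed by an index node resection", or radical surgery where the disease is in-transit. Patients with nodal disease and no MPR then have a second operation, a TLND.

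On time origins, the Endpoints section treats RFS differently from the other three time-to-event endpoints:

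- Primary: "EFS, defined as time from randomisation to melanoma progression (unresectable stage III or stage IV disease", with recurrence and death from any cause also counted.
- DMFS: "defined as the time from the date of randomisation to the date of first distant metastasis", with treatment-related and melanoma-related death also counted.
- OS: "OS, defined as time from the date of randomisation to the date of death from any cause".
- RFS: "RFS, defined as the time from the date of surgery to the date of melanoma recurrence", with treatment-related and melanoma-related death also counted.

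RFS is listed first among the secondary endpoints and carries no note that it applies to operated patients only. The same list plans to correlate pathologic response with RFS within each arm, and to report the proportion operated on within 10 weeks of the first course.

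**The concern.** Whether a patient reaches surgery is decided after randomisation and can be influenced by the assigned regimen. Progression to unresectable disease, death and toxicity can each prevent the operation. The article's Aim section describes the combination as potentially more effective but with more side effects, so these routes may operate to different degrees in the two arms.

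If the shares of patients not operated on differ, RFS compares two differently selected groups. An arm that loses more poor-prognosis patients before surgery is left with a more favourable operated group, and its RFS can look better for that reason alone. In a superiority trial with 64 patients per arm, a few patients could create or hide an apparent regimen effect on a listed secondary efficacy endpoint.

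**Working it through.** **Can an unoperated patient contribute to RFS?** The sequence is randomisation, two neoadjuvant courses, then surgery. The RFS clock starts at surgery. A patient without surgery has no time zero and cannot enter the analysis. An analysis plan cannot repair this without changing the definition or restricting its use. EFS, DMFS and OS have a time zero for every randomised patient.

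**Does the article foresee patients who are not operated on?** It does so implicitly: EFS counts progression to unresectable stage III or to stage IV disease, and timely surgery is an endpoint reported as a proportion. It gives no expected non-surgery rate, and it states no RFS figure to reproduce.

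**How large could the effect be?**

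Inputs:
- 64 patients per arm (Study design).
- 72% event-free at 24 months, the monotherapy reference EFS rate quoted in Study design, applied here to both arms so that there is no true difference.
- Share not operated on, *p*: assumed, because the article gives none.
- Every unoperated patient already counted as an event: assumed, and an extreme case.

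Formulas: the event-free proportion among operated patients is S = 0.72 / (1 − p). The apparent HR, combination against monotherapy under proportional hazards, is ln(S_combination) / ln(S_monotherapy). The small shift of the clock from randomisation to surgery is ignored.

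| p, monotherapy | p, combination | S, monotherapy | S, combination | Apparent HR |
|---|---|---|---|---|
| 5% | 5% | 0.72/0.95 = 75.8% | 0.72/0.95 = 75.8% | 1.00 |
| 5% | 10% | 0.72/0.95 = 75.8% | 0.72/0.90 = 80.0% | 0.81 |
| 10% | 5% | 0.72/0.90 = 80.0% | 0.72/0.95 = 75.8% | 1.24 |
| 2% | 12% | 0.72/0.98 = 73.5% | 0.72/0.88 = 81.8% | 0.65 |

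For the second row, ln(0.800)/ln(0.758) = (−0.223)/(−0.277) = 0.81. In patients, 5% and 10% of 64 are 3.2 and 6.4, so a gap of about three patients produces this HR.

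The assumption that all unoperated patients are events drives the size. If instead they had the same 72% event-free rate as everyone else, then S = (0.72 − p × 0.72)/(1 − p) = 0.72 for any p, and there is no shift. The distortion therefore depends both on how the non-surgery shares differ and on how the prognosis of unoperated patients differs from the rest. The article fixes neither.

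**Which operation is the date of surgery?** Study intervention describes an index node resection and, for nodal patients without MPR, a later TLND. The RFS definition does not say which one applies. If it were the TLND, time zero would depend on response.

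**The case against.** The strongest reply is that the article names no between-arm test of RFS. The only uses it spells out are correlations, including pathologic response with RFS within each arm. Pathologic response is known only after surgery, so starting the clock there is coherent for that purpose. Pre-surgical progression and death are already captured by EFS, which alone carries the sample size and the superiority claim. This stands, and it limits the point to one secondary endpoint. It does not remove the point: RFS heads the secondary endpoints of a trial designed to compare two regimens, and nothing warns against reading it as a randomised comparison.

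Four stronger readings are tempting, and the documents do not support them.

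- **That MPR excludes unoperated patients.** The text "MPR, defined as ≤10% viable tumour cells in the excised tumour" is a pathology threshold. It states no denominator, and unoperated patients can be counted as not having MPR. An article commonly leaves that choice to the full protocol or analysis plan.
- **That the RFS clock starts at different times in the two arms.** A reader might infer this from "combination therapy administered at 3-weeks interval" set against the 4-week interval for monotherapy. These are dosing intervals, which place the second dose about one week apart. The article gives one 10-week surgery window for both arms and no surgery dates by arm.
- **That RFS will favour a particular regimen.** More toxicity and less early progression on the combination act on non-surgery in opposite directions, so no direction can be established.
- **That a known share of early events is lost.** Assuming 3% to 10% unoperated means roughly 2 to 6 of 64 patients. Against 0.28 × 64 = 17.9, about 18 events by 24 months, that is 2/18 = 11% to 6/18 = 33%. The non-surgery rates are assumed, and each unoperated patient is taken to be an event. Surgery lost through toxicity is not in itself an EFS event, so these figures are upper bounds for those rates.

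**Conclusion.** The point holds for RFS. As defined, it cannot include randomised patients who are never operated on, so a between-arm RFS comparison is conditional on surgery and is not a randomised comparison. That follows from the stated definition and needs no assumption.

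The size and direction of any bias cannot be derived from the article. Under the extreme assumption that every unoperated patient is already an event, with no true difference and 72% event-free in both arms, the apparent HR runs from 0.65 to 1.24 over the assumed shares. It is 1.00 when the shares are equal, although even then the comparison is not protected by randomisation. Milder assumptions about unoperated patients shrink the shift.

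The primary EFS analysis is unaffected, as are the sample size and the comparisons of DMFS and OS from randomisation. For MPR there is no demonstrated error, only a denominator worth stating.

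**What to change.** In the protocol and the analysis plan:

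1. Label RFS as conditional on surgery and descriptive, and report the number of randomised patients in each arm who were not operated on, with reasons.
2. Keep RFS for the planned within-arm correlation with pathologic response.
3. State which operation, index node resection or TLND, starts the RFS clock, and say the same for in-transit surgery.
4. Base between-arm time-to-event efficacy statements on EFS, DMFS and OS, all measured from randomisation.
5. As a clarification only, state that MPR is calculated over all randomised patients, with no surgery counted as no MPR, unless the full protocol already says so.

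The cost is a wording change and one fewer inferential secondary endpoint. Sample size and treatment do not change. The Trial status section reports that all sites had begun enrolling as of December 2025 with a planned accrual of two years, so the change can be made before any outcome comparison.

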### Study design

The study is a phase III superiority trial comparing neoadjuvant anti-PD-1 monotherapy to anti-CTLA-4/anti-PD-1 combination therapy in patients with resectable stage III–IV melanoma with EFS as the primary endpoint. The sample size and power calculations are based on a two-sided type 1 error of 5% and a statistical power of 70%. A power of 70% was selected as a deliberate balance between the risk of a false-negative conclusion and the feasibility constraints imposed by a limited recruitable population and event accrual within a reasonable study timeframe. Included patients are stratified according to the presence or absence of in-transit metastasis. Randomisation is 1:1 with a total sample size of 128 subjects (64 per arm), with a total number of 85 events required to detect a difference in EFS of 13% or higher between the two groups. This is based on indirect cross-trial comparison of 24-month EFS rates between neoadjuvant pembrolizumab in SWOG S1801 (EFS 72% at 24 months) and neoadjuvant ipilimumab+nivolumab in NADINA (EFS 77% at 24 months). However, this cross-trial difference is expected to underestimate the true regimen effect due to differences in patient populations, perioperative systemic therapy exposure, and follow-up structures. On this basis, SWE-NEO prespecifies a clinically meaningful absolute EFS difference of 13%, representing a benefit magnitude that would justify the additional toxicity of the added CTLA-4 blockade and remains conservative relative to the ~20–25% absolute EFS gains observed when neoadjuvant strategies are compared with adjuvant-only approaches. Included patients are stratified for in-transit metastases. The anticipated accrual time is 2 years, and the follow-up period is 5 years.

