### Ethical consideration

In resectable stage III melanoma, both neoadjuvant PD-1 inhibitor monotherapy and PD-1 and CTLA-4 inhibitor combination have been shown to result in improved EFS and DMFS compared to adjuvant-only treatment. As of December 2025, neither regimen has been approved by the EMA or the FDA. However, in Sweden, both these regimens have been approved for neoadjuvant treatment in resectable stage III melanoma. The PD-1/CTLA-4 inhibitor combination is potentially more effective, but also associated with increased toxicity and higher treatment costs. In patients presenting with resectable stage III melanoma, acceptance of the risk of serious, life-threatening, or chronic side effects is generally lower than in the setting of inoperable metastatic disease. Therefore, it is possible that PD-1 inhibitor monotherapy regimen is sufficient in this clinical setting. It is therefore essential to study this benefit/risk balance to determine which treatment strategy is most beneficial. In addition, translational analyses aim to identify biomarkers that may guide treatment selection for individual patients.

Patient representatives from the Swedish melanoma patient association (Melanomföreningen) were consulted during protocol development to ensure patient relevance and acceptability, and they expressed support for the final study design. The study will be conducted in accordance with Good Clinical Practice (GCP) guidelines and the Declaration of Helsinki. All participants will receive oral and written information regarding risks of participation and their right to withdraw from the study at any time. All participants are required to provide signed and dated written informed consent (available in the Supplementary Material) prior to participation. The trial protocol is reported in accordance with the SPIRIT guidelines for clinical trials (see Supplementary Material). The trial was approved on April 30th, 2025, by the EMA Clinical Trials Information System (CTIS) (trial ID: 2024-519593-39-00) and by the Swedish Biobank Authority. ClinicalTrials.gov identifier is NCT06794775, registered on January 22nd, 2025.

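### The only adverse-event endpoint listed counts treatment-related events alone, which in an open-label trial puts the toxicity comparison at risk of differential attribution; an all-cause comparison should be added

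*Protocol article*

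**What the plan says.** The Endpoints section of the protocol article sets out the secondary endpoints in what reads as a complete list. One of them concerns adverse events: "Frequency and duration of all grade and grade 3–5 treatment- related adverse events (AEs", "graded according to Common Terminology Criteria for Adverse Events (CTCAE) 5.0". No endpoint for adverse events or serious adverse events regardless of cause is listed. The same section has one other morbidity endpoint, "Surgical complication rates graded according to Clavien-Dindo surgical classification", and both EFS and OS count death from any cause.

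The Aim section describes a "phase III randomised controlled multi-centre open-label trial" and says that the "PD-1/CTLA-4 inhibitor combination is potentially more effective but also associated with more side effects".

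Under Study intervention, both arms receive nivolumab before surgery, with ipilimumab added in one. Patients with a major pathologic response (MPR) then stop treatment. Node-positive patients without it go on to lymph node dissection and adjuvant nivolumab or, with a BRAF V600E mutation, dabrafenib and trametinib.

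Toxicity is part of the question the trial asks. Study design explains the 13-point EFS target as "representing a benefit magnitude that would justify the additional toxicity of the added CTLA-4 blockade", and Ethical consideration states: "It is therefore essential to study this benefit/risk balance to determine which treatment strategy is most beneficial".

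**The concern.** An endpoint limited to treatment-related events has two steps: the event is recorded, and then someone decides whether treatment caused it. Randomisation makes the arms comparable at entry but does not protect a classification made afterwards with the arm known. CTCAE standardises severity, not causality. If the assessor expects more toxicity from the combination, an ambiguous event may be called related more often in that arm.

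The judgement is also hard here. A patient may have had neoadjuvant immunotherapy, one or two operations, and then a second course of immunotherapy or targeted therapy. The endpoint does not say to which of these an event must be related. If MPR rates differ between arms, later drug exposure differs as well, and so does what has to be attributed.

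At stake is the adverse-event side of the benefit/risk comparison. The primary efficacy endpoint counts death from any cause and needs no judgement on drug causality. The adverse-event endpoint depends on that judgement throughout.

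**Working it through.** No sample size, event count or power figure in the article bears on this point, so there is no stated figure to reproduce. The only document input is 64 patients per arm (Study design). All other inputs below are assumptions, chosen to show what size of error is possible.

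**Illustration 1: events of uncertain cause.** Let u be the share of patients in each arm with a grade 3–5 event of uncertain cause, equal in both arms. Let c and m be the probabilities that such an event is called related on the combination and on monotherapy.

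Spurious difference = u × (c − m); patients = 64 × u × (c − m).

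Assumed ranges: u 10–30%, c 70–80%, m 40–50%.

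| u | c | m | Difference | Patients of 64 |
|---|---|---|---|---|
| 0.10 | 0.70 | 0.50 | 0.10 × 0.20 = 2 points | 1.3 |
| 0.10 | 0.80 | 0.40 | 0.10 × 0.40 = 4 points | 2.6 |
| 0.30 | 0.70 | 0.50 | 0.30 × 0.20 = 6 points | 3.8 |
| 0.30 | 0.80 | 0.40 | 0.30 × 0.40 = 12 points | 7.7 |

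The range is 2 to 12 points, or about 1 to 8 patients.

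**Illustration 2: all grade 3–5 events.** Let both arms have the same true all-cause rate p. Assume 90% of events are called related on the combination and 60–80% on monotherapy. The last column is the normal-approximation chance that a two-sided 5% test of two proportions, 64 per arm, shows a nominally significant excess on the combination. Without bias it is about 2.5%.

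| p | Monotherapy, related | Combination, related | Difference | Chance |
|---|---|---|---|---|
| 0.20 | 0.20 × 0.80 = 16% | 0.20 × 0.90 = 18% | 2 points | 4.9% |
| 0.30 | 0.30 × 0.70 = 21% | 0.30 × 0.90 = 27% | 6 points | 12.1% |
| 0.40 | 0.40 × 0.60 = 24% | 0.40 × 0.90 = 36% | 12 points | 31.5% |

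In both illustrations the true all-cause rates are equal, so an all-cause comparison has an expected difference of 0.

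**Against random error.** With 64 per arm and rates of 20% and 30%, the 95% half-width is 1.96 × √(0.20 × 0.80/64 + 0.30 × 0.70/64) = 14.9 points. A bias at the top of the range would be nearly as large as the random error, and the confidence interval would not show it.

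**The case against.** The strongest reply is that treatment-related events are a common and useful endpoint, that a journal article condenses its protocol, and that all-cause tables and causality procedures belong in the full protocol or SAP, neither of which is shown. In part this stands: the unseen documents may collect all events and may describe how causality is reviewed. But the restriction is written into the endpoint definition. Collecting all events would not change which comparison is named, and would make the addition cheaper.

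A reader might infer more than the article supports, in four ways:

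- **That investigators who know the arm do the attribution.** The article does not say who judges relatedness. An unmasked assessor is a likely inference from the open-label design, no more.
- **That the whole harm assessment is compromised.** It is not. Clavien-Dindo complications, surgery within 10 weeks of first treatment, and all-cause death need no drug attribution. The first two and death do not, however, measure non-fatal drug toxicity, which is the harm at issue.
- **That bias would carry straight into the benefit/risk conclusion.** The article states no formal benefit/risk rule or toxicity threshold, and the 13-point EFS target is not recalculated from observed events. The endpoint informs that judgement but does not determine it.
- **That the bias is large and goes against the combination.** Neither is shown. Both arms receive nivolumab, so an event can plausibly be drug-related in either, and the article has no evidence for an attribution gap of 20 to 40 points.

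It is also fair to say that all-cause counting is no complete cure. Eliciting and grading events remain unblinded. Over the whole strategy, the counts would include dissection morbidity and would reflect unequal adjuvant exposure and surveillance. This argues against replacing the treatment-related endpoint, but not against adding to it.

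**Conclusion.** The point holds as a risk of bias in one stated endpoint. The only adverse-event endpoint listed requires a causal judgement that is likely to be made with the arm known, in a trial that asks whether added efficacy is worth added toxicity. The article shows neither that bias will occur nor how large it would be. On the assumed inputs the spurious difference is 2 to 12 points, about 1 to 8 of 64 patients per arm. With no difference in attribution between arms it is zero. The endpoint is not wrong in itself; its weakness is that it stands alone. This should be changed, but it does not affect the primary analysis.

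**What to change.** Extend the endpoint to include the frequency and duration of all-grade and grade 3–5 adverse events regardless of attribution, graded by CTCAE 5.0 and compared by randomised arm from first study treatment. Report it for two periods: the neoadjuvant period up to surgery, and the whole treatment strategy. The first is free of differences in later treatment; the second shows the full burden of each strategy. State how the first period ends for patients who are not operated on. Keep treatment-related events beside both.

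The cost is one endpoint line and one more table set, with no added patients or visits if all adverse events are already recorded, as is usual in a drug trial under GCP. The downsides are some background and surgical events in the all-cause counts, partly overlapping the Clavien-Dindo endpoint, and reporting and grading that remain unblinded. According to Trial status, all three sites have begun enrolment, so the change should be made soon and before any comparative safety data are seen.
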